Regarding training and support, internal implementation teams in both groups will receive manualized pre-implementation training on how to support and deliver GlobalConsent. Implementation teams at HIS universities will receive more intensive training and support than those at LIS universities to implement the additional strategies, described above, including pre-implementation leadership training to champion GlobalConsent with internal and external stakeholders.

Our four specific aims are to:

**Aim1. Compare implementation (barriers, facilitators, modifications**) of delivering GlobalConsent in LIS versus HIS groups [36]. Separate focus group discussions with university implementation teams and the purveyor/training entity (CCIHP) will identify implementation barriers, facilitators, and modifications for HIS and LIS universities. Key informant interviews with university leaders will be used to identify organizational, internal and external policy conditions that may affect implementation. A checklist to male students will identify modifications to intended program delivery at the user level.

**Aim2. Compare implementation drivers** (e.g., institutional norms) and **outcomes** (e.g., penetration) in LIS and HIS universities. Assessments will be based on repeated surveys with university leaders, implementation teams, faculty, and male students; and administrative data on program adoption and penetration among male students. We expect implementation drivers and outcomes to be more favorable in the HIS versus the LIS group over time because of the implementation efforts.

**Aim3. Compare effectiveness outcomes** (knowledge, attitudes, affect, capacities, and behavior related to sexual violence) in the LIS and HIS groups using six-monthly surveys with male university students. We expect that men in the HIS group will report more favorable, more sustained outcomes in all domains than men in the LIS group.

**Aim4. Evaluate the cost-effectiveness** of implementing GlobalConsent in the HIS group versus the LIS group. We expect that HIS will be cost-effective relative to LIS, e.g., HIS’s additional costs will be justified by the greater impact on reducing sexually violent behavior and increasing prosocial intervening behavior when compared to LIS.

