#### Train and support internal implementation facilitators and teams.

Internal implementation teams and facilitators only in the HIS group additionally will receive leadership training before implementation and external support and technical assistance (TA) during implementation. The two-day leadership training will cover skills needed to champion GlobalConsent with diverse internal stakeholder groups. Topics will cover leadership styles, managing teams, influence without authority, managing conflict, emotional intelligence, negotiation, and leading institutional change. The leadership training also will cover effective ways to facilitate a student orientation to GlobalConsent, facilitate faculty/staff town halls (outreach sessions) about sexual violence, and send effective communications to leaders on implementation progress (Table 3). On-going external support and TA will involve six one-hour quality-improvement team consultations with CCIHP to provide refresher training, discuss implementation progress and modifications, build peer networks, and discuss anonymized data on implementation progress for shared problem-solving. Consultation sessions will be recorded and later coded as part of data collection activities.

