Longitudinal focus group discussions (FGDs) will entail four discussions with each of six groups of 5–8 [57] implementation team members (one group per university; 24 FGDs total). These FGDs will provide detailed, near-real-time data on the project’s dynamic implementation context, including features of the implementation setting; modifications to GlobalConsent or implementation plans; changes in the university, local, regional, or national context that may affect implementation; and team sense-making and learning [58]. The FGD guide [46] includes open-ended questions aligned to FRAME; the rationale, timing, and guidance for each question; and probes about the use of core implementation strategies (**Appendix**). Some questions in the FGD guide are like those in the KII guide to facilitate triangulation of the data during analysis.

A brief checklist will be added at the end of every program module of GlobalConsent (**Appendix**). This checklist will be based on the Modifications and Adaptations Checklist [59, 60], a coding scheme for recording modifications to evidence-based interventions. The checklist will ask participants to self-report any modifications they made to planned use of GlobalConsent. As students cannot skip segments or modules in GlobalConsent, the checklist will focus on the following major modifications: 1) device used to view each module of GlobalConsent, 2) percentage of module watched, 3) number of sessions required to watch the module, 4) whether or not they watched part or all of each module mor than once; 5) ‘drift’ by multi-tasking or doing other things while a module was open, 6) ‘drift’ by stepping away from the computer or mobile device while a module was open, 7) extent of satisfaction with the content of the module, and 8) any comments about the module.

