### Methods in analysis to handle protocol non-adherence and any statistical methods to handle missing data {20c}

To address protocol non-adherence, we will evaluate the balance between study arms (HIS and LIS groups) based on student responses regarding any modifications to program delivery. If necessary, we will adjust for these modifications in our analysis to reduce potential bias. Moreover, we will conduct a per-protocol analysis, including only those participants who adhered to the protocol. Comparing the results of these analyses with analyses of all participants will provide insights into the impact of non-adherence.

Inadvertent missingness will be minimized at the data collection stage by pre-programming the REDCap data system to inform the participant of any missing responses and to invite them to complete their responses before proceeding to the next survey page. Sensitivity analyses will also be conducted, with missing data imputed under the assumption of missingness at random.

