**Conduct educational outreach**	**+ +**	**+ In-person technical training (one per group)** on campus-wide implementation of GlobalConsent; **discussion and demonstration** of GlobalConsent program; **standardized implementation manual**	B	3 dy	Siloed depts limit campus-wide programs
**Train for leadership, prepare champions**	**+**	**+ In-person leadership training (one)** to champion GlobalConsent with internal stakeholders (leaders, implementation teams; faculty, students): leadership styles; managing teams; influence without authority; managing conflict; emotional intelligence; negotiation; leading change	B	2 dy	Skills needed to engage diverse internal stakeholders, lead change; enable local facilitators to support program sustainment
**Provide external support, on-going consultation, technical assistance**	**+**	**+ Biweekly (six) 1-hour recorded quality-improvement team webinars** to provide refresher training; assess implementation progress; assess modifications; build peer-network; provide anonymized data on implementation progress for discussion	D	6 hr	Limited time for facilitation, COVID-related dis-ruptions in workplace warrant webinar format Anonymized data due to sensitivity of topic, concerns over university reputation, and belief that sexually violent behavior may be uncommon

Notes. B=before implementation; D=during implementation; A=after implementation; C=continuous (before, during, after implementation)

**Table 4. T4:** Data Collection Methods for Implementation Assessment (Aim 1)

Method	Stakeholder Group	N	# of Rounds	Total
Team reflections with CCIHP	CCIHP (external facilitators)	NA (external)	12	12
Key informant interviews (KIIs)	University leaders	5 per university 15 per IS group 30 total	2	60
Focus group discussions (FGDs)	University implementation teams	1 per university 3 per IS group 6 total	4	24
Modification checklist	First-year male student participants	637 per university 1910 per IS group 3821 total	1	~3821

Note. IS=implementation strategy

**Table 5. T5:** Implementation Outcomes and Potential Drivers Aligned with RE-AIM [24, 25] and Proctor et al [32] for Comparison Across Implementation Strategies Groups

Construct	Measures	# items	Study samples	# waves

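### The arm-balance check on non-adherence uses a checklist that only men who finish a module can answer, and the coded HIS-only consultations are not reconciled with the Aim 1 sources

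*Protocol article*

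**What the plan says.** **Student level.**

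- Objectives {7}, Aim 1: "Compare implementation (barriers, facilitators, modifications" in LIS versus HIS. A student checklist is the named tool at user level.
- Outcomes {12}, Aim 1: "A brief checklist will be added at the end of every program module of GlobalConsent". Students cannot skip segments or modules. Items include the share of the module watched and drift while it was open.
- Non-adherence and missing data {20c}: "we will evaluate the balance between study arms (HIS and LIS groups) based on student responses regarding any modifications to program delivery", with adjustment for these modifications if judged necessary.
- Intervention description {11a}: HIS students also get an in-person orientation, monthly learning sessions, weekly instead of fortnightly reminders, and a prize lottery on completing the program.
- Table 4 gives the checklist sample as "637 per university 1910 per IS group 3821 total", in one round, with an approximate total of 3,821.
- Adherence {11c}: the IT company passively records module opening and time open. Under Aim 2 its records also show who consents and who completes the program.

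**Team level.**

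- Intervention description {11a}: HIS teams alone receive "six one-hour quality-improvement team consultations with CCIHP to provide refresher training, discuss implementation progress and modifications". Of these the protocol says: "Consultation sessions will be recorded and later coded as part of data collection activities". Table 3 gives their purposes as "to provide refresher training; assess implementation progress; assess modifications; build peer-network".
- Qualitative data analysis (Aim 1) names reflection notes, field diaries, and transcripts of key informant interviews (KIIs) and focus group discussions (FGDs). Table 4 lists reflections, KIIs, FGDs and the checklist. Neither names the consultation recordings.

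**The concern.** A check on non-adherence should cover the men who did not adhere. Here the clearest non-adherers, those who never start or who abandon a module, supply no answers for what they did not finish. Whether a man answers is therefore tied to the behaviour being measured. Because completion is what the HIS bundle tries to change, the selection can differ by arm. The check might then find imbalance where the men behave alike, or miss it where they do not, and any adjustment in {20c} would carry the error into the effectiveness analysis.

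At team level, data on an outcome compared between arms are collected in one arm only, and the protocol does not say what they are for. If they entered the LIS–HIS contrast, HIS would be observed more often than LIS.

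**Working it through.** **1. Table 4's figure.** Inputs: 4,776 eligible men and 80% participation (Sample size {14}); two arms; six universities.

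- 4,776 × 0.80 = 3,820.8, so 3,821 in total
- 3,820.8 / 2 = 1,910.4, so 1,910 per arm
- 3,820.8 / 6 = 636.8, so 637 per university

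The figure is reproduced. It is the expected number of participants, with no reduction for men who do not start or do not finish. The program has six modules (Abstract) and the checklist follows each one, so one round does not describe it. The most that could be returned is 3,821 × 6 = 22,926 forms.

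**2. Who can answer.**

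| Student | Checklists returned |
|---|---|
| Consents, never starts | 0 |
| Stops during module 1 | 0 |
| Finishes k modules, stops in the next | k |
| Finishes all six | 6 |

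The item on the share of a module watched is put only to men who have reached its end.

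**3. What selection could do (illustration; all rates assumed).** Take one module. Let a share cL finish it in LIS and cH in HIS, with cH at least cL. Suppose men who would finish under either bundle report drift at 30%, and all other men would report it at 60% if asked. Behaviour by type of man is the same in both arms.

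- Reported in LIS: 30%
- Reported in HIS: (cL × 0.30 + (cH − cL) × 0.60) / cH
- True in both arms: cL × 0.30 + (1 − cL) × 0.60

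| cL | cH | LIS reported | HIS reported | True, both arms |
|---|---|---|---|---|
| 80% | 80% | 30% | 30% | 36% |
| 70% | 80% | 30% | 33.75% | 39% |
| 60% | 80% | 30% | 37.5% | 42% |
| 50% | 80% | 30% | 41.25% | 45% |

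For the last row: (0.50 × 0.30 + 0.30 × 0.60) / 0.80 = 0.33 / 0.80 = 41.25%. A false arm difference needs two things together: completion that differs by arm, and added finishers who differ from the others. Without either it is zero. If the added finishers drifted less, its sign would reverse.

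**4. Team-level sources, per university.**

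| Source | LIS | HIS | Named for Aim 1 analysis? |
|---|---|---|---|
| FGDs | 4 | 4 | Yes |
| KIIs (5 leaders × 2) | 10 | 10 | Yes |
| Coded consultations | 0 | 6 | No |

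The twelve reflections with CCIHP, the training organisation, cover both groups and are not divided by university. On the FGDs and KIIs the count is 14 versus 14. If the recordings were added it would be 14 versus 20. The protocol does not say whether consultations are held per university or jointly.

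**The case against.** **Student level.** The checklist is the same in both arms and follows every module, so a man who finishes one module and later stops still contributes. Non-start and non-completion are recorded elsewhere, in the IT logs and the Aim 2 adoption and penetration outcomes. Table 4's total is an approximate planning number. All of this is correct, and the last point means that equal numbers per arm in Table 4 do not contradict an expectation of higher completion in HIS. But {20c} rests the balance check on student responses, not on the logs, so those records do not repair it. Relabelling non-completion as a modification would be a matter of preference, since penetration is already an Aim 2 outcome.

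**Team level.** A reader might infer that the Aim 1 comparison is biased and that HIS will show more modifications because it is watched more closely. The documents do not support that:

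- The FGDs and KIIs named for the analysis are equal by arm, and the recordings are not among the named sources. They could be meant for describing HIS only.
- The reflections cover both groups, and nothing says that they carry consultation content. That CCIHP learns more about HIS from its biweekly contact is plausible but not stated.
- LIS contact is not purely passive. It includes three days of training, answers to website questions, and activity checks at invoicing.
- Aim 1 is a qualitative matrix synthesis without a rate to be biased. The consultations are also meant to encourage adherence ({11b}), which could lower HIS modifications.

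What stands is that {11a} calls the coded sessions study data while the Aim 1 sources omit them, and no rule keeps them, or reflections drawn from them, out of the contrast.

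**Conclusion.** The student-level point holds. The {20c} balance check and possible adjustment leave out men who never start and, for the unfinished module, men who stop midway. They may also compare differently selected men by arm. The expectation that completion differs comes from the design of HIS. That finishers differ from non-finishers is an assumption. The protocol gives no completion rates, so the size is unknown. Under the rates assumed above, the false difference runs from 0 to about 11 percentage points. Table 4's 3,821 is arithmetically right, but it is the number eligible to answer, not the number expected to.

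The team-level point is narrower: {11a} and Table 3 must be reconciled with the Aim 1 analysis text and Table 4. It is a risk of unequal ascertainment, not a demonstrated bias.

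**What to change.** 1. In {20c}, base the non-adherence balance check on the IT company's logs for all consenting students: module opened, time open, module finished. The protocol names the first two and program completion. That completion is also held per module should be confirmed with the company.
2. Report checklist results per module, with the numbers starting and finishing that module by arm.
3. In Table 4, restate 3,821 as the maximum number eligible, and show the checklist as repeated after each of six modules.
4. State that the coded consultations, and reflection content drawn from them, are used to describe HIS only. Base the LIS–HIS contrast of modifications on sources held equally in both arms (FGDs, KIIs).

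The cost is wording in Aim 1, Table 4 and {20c}, plus tabulation of records already collected. The downside is that the HIS sessions no longer add to the between-arm contrast.

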### Criteria for discontinuing or modifying allocated interventions {11b}

CCIHP will encourage adherence to the implementation plan of the LIS and HIS groups in response to any questions that are posted to the GlobalConsent website regarding deviations to the implementation plan. CCIHP also will encourage adherence to the implementation plan of the HIS group in its regular consultative meetings, when it provides technical support. The study team will conduct regular focus group discussions with implementation teams to monitor modifications to implementation strategies that LIS and HIS implementation teams may apply (Aim 1). The decision to discontinue a student’s participation in GlobalConsent will be made based on an adverse events protocol that is described elsewhere in this study protocol.

### Strategies to improve adherence to interventions {11c}

To improve implementation-team adherence to the LIS and HIS implementation strategies protocols, Emory and CCIHP will establish deliverable-based contracts with each university clarifying the terms of reference (TOR) and payment schedule for mutually agreed implementation activities. At the time of implementation team training, each team member at each participating university will assume specific roles and responsibilities, and a team supervisor will be responsible for overseeing the activities of all implementation team members. The completion of all activities will be assessed at the time that each university invoices CCIHP for its work, and payment of invoices will be based on the demonstrated completion of implementation activities in the TOR.

To support students’ adherence to the GlobalConsent program in the HIS group, the contracted IT company (with support from internal implementation team members) will send students weekly email and/or text reminders to complete each program module. In the LIS group, the contracted IT company, with support from internal implementation team members, will send students email and/or text reminders once every two weeks to complete each program module. Students will be offered to enter their unique ID into a lottery to win a small prize for completing each module. Student adherence to program participation will be monitored with a short survey after each program module and with passive monitoring by the IT company delivering the program (times module opened, time spent with module open).

### Relevant concomitant care permitted or prohibited during the trial {11d}

There is no concomitant care that is specifically permitted or prohibited during the trial.

### Provisions for post-trial care {30}

A case management protocol for post-trial care is applied to all students who participate in the GlobalConsent program and each survey wave. First, near the end of each survey, all student participants are provided a comprehensive resource list of local fee-based and non-fee-based services. This resource list is provided to all participants. Second, after providing the resource list, all participants are asked to report their level of distress (1=not at all distressed to 10=extremely distressed) and the manageability of their reported distress (0=manageable, 1=manageable with resources, or 2=not at all manageable). Any participant who reports extreme distress (=10) or “not at all manageable” distress (=2) regardless of the distress level reported will receive an emergency contact number in REDCap and will be offered the opportunity to follow-up with a professional counselor. The message will read: “Your wellness is important to us, and someone outside of the study can follow-up with you, if you wish. They will have no information about your answers. Please indicate how you are most comfortable seeking help.” If the participant reports that they want someone to follow-up with them, their ID will be shared with a non-study staff member at CCIHP. Within three days of the participant’s responses being submitted in REDCap, this staff member will introduce the case and his contact information to an expert (clinical psychologist) who is responsible for supporting participants in the relevant geographic region (North, Central, South). Within 1–3 days after the expert receives the participant’s contact information, the expert will contact the case via phone call to introduce themself and their professional background, and to set an appointment for an online or in-person assessment. The expert will attempt to contact the participant over three days. If unsuccessful, the expert will re-confirm or correct the contact details, and attempt contact again. If successful, the expert will schedule an appointment and complete an assessment, including whether the unmanageable distress was study-related. The expert will make recommendations regarding strategies for intervention, including fee-based and non-fee-based services. If the case refuses support at the time of the expert’s call, the expert will inform the case about available fee- and non-fee-based services. In all cases, the expert will report the general outcomes of their follow-up attempts and whether any unmanageable distress was attributable to the study or the intervention. The study team will report the findings of all adverse events (extreme distress and/or unmanageable distress, regardless of the distress level reported) to the responsible IRBs, independent data safety and monitoring board (DSMB), and study sponsor, in accordance with the timetable required by the National Institutes of Mental Health Reportable Events Policy [55]. In each case, determination about continuation or discontinuation of the program will be made by these parties independently.

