#### Online quantitative surveys (Aims 2–3).

Eligible participants in the quantitative portions of the study will read an informed consent form provided in an online REDCap survey [49]. Eligible participants will indicate with check boxes that they have read each paragraph in the consent form and will be provided with a phone number to call if they have any questions that a non-study team member can answer. After all paragraphs are checked, the eligible participant will be invited to provide a response to confirm their consent or non-consent to participate in the study. Informed consent will be obtained before participants will be allowed to view and to participate in the online REDCap survey for which they are eligible (**Appendix**).

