#### Survey-based data collection (Aim 1 checklist; Aims 2–3).

Survey-based data from all target populations will be collected via REDCap [49], a HIPAA-compliant, web-based data system that allows for the secure collection, transfer, storage, and analysis of study data. Customized surveys will be piloted with individuals like the focal populations but at non-study universities to gauge acceptability, inform final revisions, and assess timings to minimize respondent burden (e.g., 10–15 minutes for each leader, faculty, and implementation team survey; 16 minutes for each student survey). The survey implementation protocol described, above, under “Recruitment” will be followed for at each survey wave for faculty, implementation teams, and students to maximize their participation at baseline (~80%) and retention at endline (~90%), based on prior experience surveying students in Vietnam [51].

Measurement time points will vary for each target sample, according to the project timeline (Figure 2). Leaders will be assessed twice, once before and once after implementation. Implementation teams will be assessed quantitatively at four time points: once before the start of any implementation activities, and once immediately before, during, and after implementation of GlobalConsent. Other data on the implementation will come from administrative records collected by the IT company that is responsible for delivering GlobalConsent. Faculty will complete one assessment before implementation (Year 1) and two after the planned 12-week delivery period of GlobalConsent (Years 3, 5). Three surveys will be administered to students at six-month intervals before the planned 12-week delivery period of GlobalConsent, and three six-monthly surveys will be administered at the same interval after implementation, for a total of six assessments. At each occasion, we will send to students’ smartphones an encrypted link to a REDCap survey with ~189 questions measuring two primary behavioral outcomes and seven cognitive/knowledge, attitudinal/belief, affective, and capacity-related secondary outcomes validated in the efficacy trial [33, 50, 51] (Table 6). Secondary outcomes that are included align with our theory of change (Figure 1) and showed evidence of mediation in the trial [50]. A short modification checklist of 5–10 questions will be administered at the end of each GlobalConsent program module to understand participants’ engagement and satisfaction with the module (Table 4).

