### Plans to promote participant retention and complete follow-up {18b}

To maximize retention across occasions, we will conduct brief cognitive interviews and pilot all REDCap surveys in similar populations at other universities in Vietnam. These steps will ensure comprehension of the questions as intended, acceptability of the questions, and appropriate length to minimize participant burden. Implementation teams and the REDCap application will administer a standard protocol of internal and automated reminders to complete each survey. To clarify institutional support and to encourage participation, leaders and/or implementation team members at each participating university will send invitation letters via email prior to survey launch. After the initial survey launch, a standard protocol of follow-up communications will be implemented for all survey waves with faculty, students, and implementation team members to maximize enrollment and retention. University leaders will receive a survey link from the CCIHP study member who conducts their KII, who will confirm individually that they have completed the survey. In addition to implementing a systematic protocol for outreach, participants who complete at least part of each survey will be compensated for their time. Also, for students, we will offer options to enter a lottery to win prizes (a smartphone) after completing all pre-implementation surveys and then all post-implementation surveys.

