#### Responsibilities and review.

The DSMB will review the DSMP and study protocol before the first participant’s enrollment to establish a charter that clarifies what data points will be monitored, how they will be monitored, and the monitoring schedule. The DSMB review will include, at a minimum: enrollment data, safety data, and data integrity. As this study is blinded, the DSMB may be blinded or unblinded to the intervention assignment but will be able to be unblinded if needed.

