#### Metrics for review.

The study team will provide descriptive statistics for the DSMB’s review at each of its meetings. Descriptives will cover questions from the following survey modules for male students and will include information about missingness/non-response.

Demographics (once at baseline)Knowledge about sexual violence (from each survey wave)Knowledge about sexual consent (from each survey wave)Rape Myths (from each survey wave)Skills to engage in healthy communication (from each survey wave)Rape empathy (from each survey wave)Readiness to intervene (from each survey wave)Bystander intervention strategies (from each survey wave)Sexual Experiences (from each survey wave)Single question on distress (SRQ-20 item 6)

In addition to the above enrollment and safety data, the study team will provide data to the DSMB on the following study-related variables from male students:

Participation rates in the survey, by universityRetention rates in the survey at each wave, by universityParticipation rates in the program, by universityRetention rates in the program, by university

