A comprehensive list of resources will be made available to every participant toward the end of every survey to ensure that all participants have access to confidential care. In addition, adverse events among students who are receiving the GlobalConsent program will be identified with a series of self-report questions at the end of every survey. These questions will identify the level of distress the participant is experiencing in the moment and its self-reported manageability. Any participant who reports extreme distress (level 10 on a scale of 1–10) or any level of distress that they identify as “not at all manageable” will be given a contact number for an experienced professional for immediate support. Such participants also will be invited to have a non-study staff member connect them with an experienced professional for a confidential assessment and then appropriate referrals.

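### The resource list and the distress questions that identify student adverse events come only near the end of each survey, so on the text shown a man who stops early and does not return gets neither at that wave.

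*Protocol article*

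**What the plan says.** Protocol article, Provisions for post-trial care {30}: "near the end of each survey, all student participants are provided a comprehensive resource list". The two questions, on level of distress and on how manageable it is, follow the list. An extreme or unmanageable answer triggers the emergency number and the offer of a counsellor.

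Adverse event reporting and harms {22} repeats this order. The list comes "toward the end of every survey to ensure that all participants have access to confidential care", and adverse events among students receiving the program "will be identified with a series of self-report questions at the end of every survey".

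Survey-based data collection (Aim 1 checklist; Aims 2–3) describes "a REDCap survey with ~189 questions measuring two primary behavioral outcomes" and gives about 16 minutes for each student survey. There are six waves.

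Plans to promote participant retention and complete follow-up {18b} says that the implementation teams and REDCap "will administer a standard protocol of internal and automated reminders to complete each survey". It also says that men who complete only part of a survey are still paid.

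Metrics for review lists the student modules for which the DSMB gets descriptive statistics, including missingness. The only distress entry is "Single question on distress (SRQ-20 item 6". Participation and retention rates by university are added.

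**The concern.** The list is the one form of support offered to every student whatever his answers, and section {22} states its aim as access to care for all. The two questions are how the protocol says student adverse events are found, and the emergency number and counsellor offer depend on the answers. Both sit behind the content that might distress someone, including 45 items on sexually violent behavior. The article itself lists mild distress from participation and recall as an expected adverse event.

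At stake is whether support and detection reach men who do not finish, and whether the DSMB can see how many started surveys lack an answered screen when it reads the count of distress reports.

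**Working it through.** The check is mainly a reading of the text.

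1. **Order within the survey.** Sections {30} and {22} agree: outcome content first, then the list, then the two questions.

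2. **Whether break-off is foreseen.** Section {18b} pays partial completers, so unfinished surveys are expected. No rate is given.

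3. **Whether another described route delivers the list or the screen.**
   - Data management {19} describes a missing-response check at the bottom of each page. It cannot reach a man who has left.
   - The checklist after each program module covers device, viewing, drift, satisfaction and comments, not distress.
   - Under Online quantitative surveys (Aims 2–3), participants are "provided with a phone number to call if they have any questions". This is for questions at consent and is neither the list nor a distress screen.
   - Adverse Events Management promises referral after a stress-related event, but by the procedures already described, which start from the same end-of-survey questions.
   - Nothing shown supplies the list on exit or by message after an unfinished survey.

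4. **What the DSMB sees.** Missingness is promised for the listed modules, most of them at each wave, so general break-off would show. The two questions of section {30} are not listed. The SRQ-20 item has no stated position in the survey and is not tied to the referral trigger. Non-response to the adverse-event screen itself is therefore not promised.

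5. **Scale only.** Inputs from Sample size {14}: 4,776 eligible men, 80% participation, 90% retention.
   - Participating: 4,776 × 0.80 = 3,821 (the total that Table 4 gives).
   - Retained: 4,776 × 0.80 × 0.90 = 3,439 (the figure under Power for analyses of student data).
   - Per 1% unfinished and not resumed: 3,821 × 0.01 ≈ 38 men; 3,439 × 0.01 ≈ 34 men.

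   These totals may or may not count men who start and do not finish; the article does not say. No break-off rate is assumed.

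**The case against.** The case on the other side has several parts.

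- **A screen for distress caused by questions has to follow the questions.** This stands, and the fix leaves the screen where it is. It does not explain why the list cannot also be reached earlier.
- **The burden is modest and follow-up is active.** The survey takes about 16 minutes and is piloted for length. The data-collection section applies the survey protocol under Recruitment to students at each wave; as detailed there for faculty, it includes repeated reminders, SMS and calls. Six waves give six chances to see the list. This stands as mitigation: it lowers the number missed, but does not reach a man who never returns at that wave.
- **The Appendix forms and consent text are not shown and may carry support contacts.** This stands as a limit on the first half of the point. Where the article states a placement, though, the placement can be assessed.
- **The DSMB charter may add data points.** The article says "The DSMB review will include, at a minimum: enrollment data, safety data, and data integrity". This stands too, and makes the charter the natural place for the addition.

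A reader might go further and infer that the DSMB could not tell few reported events from few answered screens. The documents do not support that, because missingness across the listed modules, with participation and retention rates, would show how much break-off occurs. A reader might also see a contradiction with the statement that every participant gets the list. That sentence can be read as meaning whatever his answers, so none is shown. Nor does anything in the article show that men stop because of distress, or that break-off differs between arms.

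**Conclusion.** The point holds as a limited weakness in participant safety. The stated placement misses the protocol's own aim for the list, at that wave, for men who break off and do not come back; the same men are not screened for adverse events at that wave. Separately, non-response to the two screening questions is not among the metrics promised to the DSMB.

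The size is unknown. The 34 to 38 men per 1% of unfinished surveys is arithmetic for scale, not an estimate. The conclusion rests on the article as shown: if the Appendix forms already give the list early, the first part is settled by saying so, and the DSMB part remains. This is a cheap improvement to a stated arrangement and does not call the trial's comparison into question.

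**What to change.** 1. Make the existing resource list reachable by a link from the first survey page, identical in both arms. Alternatively, put the link in the automated reminders already sent to non-completers.
2. Leave the distress questions, the triggered emergency number and the counsellor pathway as they are.
3. Add the two distress items to Metrics for review, with the number of started surveys in which they are unanswered, at each wave and by coded arm. The DSMB charter can carry this, and the non-ordered numeric codes described under Who will be blinded {17a} preserve the blind.

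The cost is one link in a REDCap survey that is already paged and one extra line in a report that already covers missingness. The downside is a small change in survey context before men report their own behavior, which is a primary outcome. If the link is introduced mid-series, it should start at the same wave in both arms and be documented. That protects the between-arm contrast, but within-arm level changes in the interrupted time series could still be affected. Placing the link only in the reminders would limit the change to men who have not completed the survey.
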